##### EEG

On the last day of the measurement week, participants visit the lab where EEG and ECG measurements are performed during resting-state, an implicit emotion regulation task, and SART. EEG and ECG data in the lab is recorded using a BioSemi Active Two system (www.biosemi.com) with 32 electrodes positioned at the 10–20 system and eight external electrodes [64]. Data recording is done using the Actiview software, sampled at a 512 Hz frequency and stored on a shielded drive. Data is pre-processed using EEGLAB [65]. The cognitive tasks are used to study the physiological correlates during task performance, comparing PC thoughts with non-PC thoughts using the SART and studying the physiological correlates of different emotion processing strategies using the emotion regulation task. Specifically, we extract event-related potentials indicating mental effort, attention, and emotion processing and -regulation before and after interventions.

##### Questionnaires

On the last day participants are asked to complete questionnaires at home to assess symptoms via e-mail. Here, the IDS-SR, Perseverative Thinking Questionnaire (PTQ) [66], Responses on Positive Affect Scale (RPA) [31], Emotion Regulation Questionnaire (ERQ) [67], Five Facet Mindfulness Questionnaire (FFMQ) [68], Leuven Adaptation of the Rumination on Sadness Scale (LARSS) [69], and the Positive and Negative Affect Schedule (PANAS) [70] are administered. After peri-intervention measurement weeks (T2, T4), we furthermore evaluate the interventions by asking participants how they have experienced the professional training and home exercises. Questionnaire data is collected and stored using REDCap.

The measurements include four sessions of two hours in the lab and 50 min of completing questionnaires at the end of the measurement week and around 60 min per day of completing the ESM questions and performing the mobile version of the SART for four weeks in total.

## Outcome measures

### Study aim 1

Primary outcomes for the first study aim in which we will examine changes in the content and dynamics of PC after interventions are within-subject changes, comparing pre- and peri-intervention measurements, in 1) self-reported measures of the content and dynamics of PC measured with ESM and the SART (using the following variables: rumination, occurrence of off-task thinking, valence of thoughts, temporal orientation of thoughts, self-relatedness of thoughts, and stickiness of thoughts), 2) HR and HRV during PC (i.e., negative, repetitive thinking) measured with ECG during ESM self-reports, and 3) EEG characteristics during PC measured in the context of the SART.

Secondary outcome measures that will be used to explore the role of sleep on the effectiveness of interventions in reducing the vulnerability for depressive relapse are 1) within-subject changes in objective and subjective sleep (measured as total sleep time, sleep quality, sleep onset latency) using actigraphy and ESM items about sleep and 2) within-subject changes in PC following the interventions. Moreover, we will examine changes in (residual) depressive symptoms and other depression-related measurements before and after the interventions (for questionnaires see Procedure) using within-subject comparisons.

### Study aim 2

To test whether changes in PC induced by fantasizing and mindfulness are different in rMDD versus ND participants, primary outcome measures are between-group differences in individual changes between pre- and peri-intervention measurements for both interventions (fantasizing and mindfulness) measured with 1) self-reported PC measures (ESM and SART), 2) HR and HRV during self-reported PC (ESM), and 3) EEG characteristics during PC measured with the SART.

### Study aim 3

Baseline individual characteristics of 100 participants (both ND and rMDD) for examining the magnitude of changes in PC following interventions include: 1) self-reported measures of PC measured with ESM and the SART, 2) HR and HRV measured with ECG during self-reported PC measured with ESM, 3) EEG characteristics during PC measured with the SART, and 4) resting state EEG. Predictors include mindfulness, rumination, emotion regulation strategies, psychiatric history, personality, dysfunctional attitudes, and childhood trauma.

## Statistical analyses

### Study aim 1

To test whether psychological and psychophysiological indices of PC are differentially affected by fantasizing vs. mindfulness, we will examine within-subject changes in pre- and peri-intervention measurements in the dynamics and content of self-reported PC, HR and HRV during self-reported PC, and electrophysiological correlates of PC and compare those between the fantasizing and mindfulness condition. We will check whether the relationships are linear or nonlinear. If the relationships are linear, we will perform linear mixed effect models (LME). If the relationships are non-linear, we will perform generalized additive models (GAMs) [71].

To examine changes in the dynamics and content of self-reported PC after interventions, several variables of PC over time will be examined. Specifically, we will consider rumination, occurrence of off-task thinking, valence of thoughts, temporal orientation of thoughts, self-relatedness of thoughts, and stickiness of thoughts. If interventions differently affect these variables of PC, we expect to find an interaction effect between intervention (fantasizing or mindfulness), session (pre- or peri-intervention), and time (time of ESM beep). For example, we hypothesized that mindfulness increases the frequency of present thoughts (i.e., temporal orientation of thought) in contrast to fantasizing where we do not expect this. If this would be the case, an interaction effect between intervention, session, and time on the temporal orientation of thoughts would be found. After running the LMEs or GAMs, visualization of the data will be used to further study the dynamics of the different changes over time.

To examine within-subject changes in pre- and peri-intervention measurements on the physiological correlates of PC, we will examine changes in HR and HRV and EEG voltage during self-reported PC. If interventions differently affect these physiological correlates of PC, we expect to find an interaction effect between intervention (fantasizing or mindfulness), session (pre- or peri-intervention), and time (in minutes to milliseconds).

To address the secondary objective about the role of sleep on the effectiveness of interventions in reducing PC, we will be using LMEs or GAMs depending whether the data are nonlinear. If sleep plays a role in whether interventions reduce PC, we expect to find a main effect of sleep (i.e., total sleep time, sleep quality and sleep onset latency) on changes in self-reported PC after the interventions.

To study the effects of the interventions on depressive symptoms using self-report questionnaires, a repeated measures ANOVA will be used with questionnaire scores (IDS-SR, PTQ, RPA, ERQ, FFMQ, LARSS, PANAS) administered as dependent variable and intervention (fantasizing or mindfulness) and session (pre- or peri-intervention) as independent variables. If interventions differentially affect depressive symptoms, we expect to find an interaction effect between intervention and session.

### Study aim 2

To study whether changes in PC by fantasizing and mindfulness are different in individuals with rMDD vs. ND controls, we will run the same analyses as for study aim 1, but with the variable group (rMDD or ND) added as an independent variable. Specifically, to examine the differential effects of self-reported PC, HR(V), and EEG, we will include session and intervention in interaction with group as independent variables in the model. If changes in PC after interventions are different in rMDD vs. ND individuals, we expect to find an interaction effect between group, session, and intervention on self-reported PC and its (neuro)physiological correlates measured with HR(V) and EEG.

### Study aim 3

For the third objective of exploring the role of individual characteristics on the effectiveness of the interventions at reducing PC, we will use baseline individual characteristics of participants assessed by means of a set of questionnaires (e.g., mindfulness, rumination, emotion regulation strategies, psychiatric history, personality, dysfunctional attitudes, childhood trauma etc.) and correlate those with changes in 1) self-reported measures of PC measured with ESM and the SART, 2) HR and HRV during reported PC, and 3) EEG characteristics during PC measured with the SART after mindfulness and positive fantasizing interventions. When significant correlations are found, we will do post-hoc moderation analyses to see how specific individual characteristics moderate changes in PC.

For all analyses, we will use a critical *p*-value of *p* < 0.05 that will be corrected for multiple comparisons using the Benjamini–Hochberg procedure [72]. Analyses will be performed using the statistical software R*.* LMEs and GAMs allow not only fixed effects, but also random effects. Random effects such as individual variability will therefore be added as well. In case non-significant effect are found for the LME analyses, Bayes Factors will be computed to find out whether this non-significant effect can be seen as proof for the H0 hypotheses (null effects) or whether this is due to the lack of reliability in the collected data [73]. Calculating Bayes Factors is not possible for GAMs, so this will only be conducted for LME models.

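### Aim 1 names only the intervention × session × time term, yet its worked hypothesis is a difference in level, which belongs to intervention × session

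*Protocol article*

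**What the plan says.** Outcome measures (Study aim 1) defines the primary outcomes as "within-subject changes, comparing pre- and peri-intervention measurements", in self-reported PC (ESM and SART), in HR and HRV during PC, and in EEG characteristics. Statistical analyses (Study aim 1) opens by saying that these changes will be compared between the two conditions.

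The effect expected if the interventions differ is then given as follows: "we expect to find an interaction effect between intervention (fantasizing or mindfulness), session (pre- or peri-intervention), and time (time of ESM beep"). The worked example is "we hypothesized that mindfulness increases the frequency of present thoughts (i.e., temporal orientation of thought) in contrast to fantasizing", and the conclusion drawn from it is "an interaction effect between intervention, session, and time on the temporal orientation of thoughts would be found". The same three-way term is named for HR, HRV and EEG, with time running from minutes to milliseconds.

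The closing paragraph of Statistical analyses sets p < 0.05 with Benjamini–Hochberg correction. For non-significant LME effects it adds a Bayes factor, to judge whether the result supports the null hypothesis.

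**The concern.** The worked hypothesis concerns a level: how often thoughts are about the present. The primary outcome is also a level, namely the change from the pre week to the peri week. Comparing that change between two interventions is the intervention × session contrast. Adding time asks whether the contrast varies across the measurement period. The article treats the second question as the test of the first.

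If mindfulness raises present-oriented thinking from the training session onward and holds it there, the stated hypothesis is true and the stated test has nothing to detect. Such a pattern is plausible on the article's own account: Background says that both techniques act after a single session, and each intervention begins with a two-hour training. For HR and HRV, the peri-week device is worn only for the last 24 hours (ECG/ICG), so build-up across that week cannot appear within the recording.

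The stake is the inference for the primary aim. A null three-way term, followed by a Bayes factor favouring H0, could be reported as no differential effect when a difference in level exists.

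**Working it through.** **The plan's own figure.** The article gives no power or sample size for either interaction. Its aim 1 figure, n = 36, is for a one-tailed t-test on questionnaire scores with g = 0.59: 2 × (1.645 + 0.842)² / 0.59² = 35.5, so 36 (normal approximation, two independent groups). It says nothing about the three-way term.

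**Algebra.** Let D(t) be the difference between interventions in peri-minus-pre change at time t. In the full factorial linear model, D(t) = β_IS + β_IST × t. If D(t) = δ throughout, then β_IS = δ and β_IST = 0. A noise-free fit of the eight-term model with a shift of 0.5 in one peri-week cell returned 0.5 for intervention × session and 0 for the three-way term, both with centred time and with time coded 0 to 69. No variance assumption enters.

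**Power.** From the article: N = 50 rMDD and 10 × 7 = 70 beeps per week. Assumed, because the article gives none: beep-level SD 1 (the unit), and two sets of remaining values.
- Set A: B = 49 answered beeps (70% of 70), between-week SD s_w = 0.4, weekly slope SD s_s = 0.3.
- Set B: B = 70, s_w = 0.5, s_s = 0.5.

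Time is taken as position in the week, scaled from −0.5 to 0.5. For each person, form the intervention × session contrast of the four week means (two-way) and of the four week slopes (three-way), then apply a one-sample t-test.

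- SE of two-way = √[4(s_w² + 1/B)/N]. Set A: √[4(0.16 + 0.0204)/50] = 0.120. Set B: √[4(0.25 + 0.0143)/50] = 0.145.
- S = B(B + 1)/[12(B − 1)]. Set A: 4.25. Set B: 6.00.
- SE of three-way = √[4(s_s² + 1/S)/N]. Set A: √[4(0.09 + 0.235)/50] = 0.161. Set B: √[4(0.25 + 0.167)/50] = 0.183.

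Power from the noncentral t with 49 df, two-sided 5%, before multiplicity correction:

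| Differential effect over the peri week | Mean | Slope | Set A: two-way / three-way | Set B: two-way / three-way |
|---|---|---|---|---|
| Constant 0.4 | 0.40 | 0 | 90% / 5% | 77% / 5% |
| Constant 0.5 | 0.50 | 0 | 98% / 5% | 92% / 5% |
| Constant 0.8 | 0.80 | 0 | 100% / 5% | 100% / 5% |
| 0 on day 1, then 0.4 | 0.34 | 0.29 | 80% / 42% | 64% / 34% |
| Linear 0 to 0.4 | 0.20 | 0.40 | 37% / 68% | 27% / 57% |
| Linear 0 to 0.8 | 0.40 | 0.80 | 90% / 99.8% | 77% / 99% |

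Example, set A, constant 0.4: 0.4/0.120 = 3.33 on the two-way term, hence 90%; 0/0.161 = 0 on the three-way term, hence 5%. Simulations under the same settings agree to within about two percentage points.

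**The case against.** **The time profile is unknown.** There are seven ESM days but six daily exercises, attention to thoughts comes only on day 5, and the figure with the detailed timing is not visible. A late or growing effect is plausible, and the aim includes dynamics. This stands: a day-2 onset gives the three-way term 34% to 42% power at a 0.4 shift, and with a linear build-up the three-way term beats the two-way. It is a reason to name both terms, not a reason to rely on the three-way alone.

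**The model probably contains the two-way term.** The article never says that lower-order terms are dropped, and aim 2 extends the same analyses to group × session × intervention without time. This also stands. A reader might infer that the plan fixes a rule that declares no differential effect when the three-way term is null. The text does not go that far: it says what is expected, and it ties Bayes factors to non-significant LME effects generally. But no sentence attaches an aim 1 conclusion to intervention × session for these outcomes.

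**GAMs.** With centred smooths a level shift sits in the parametric term, whereas an uncentred difference smooth would absorb it. The exact zero is therefore a statement about the LME.

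**Questionnaires.** Since the plan there says "we expect to find an interaction effect between intervention and session", a reader might infer that it contradicts itself across outcomes. It does not. Questionnaires are completed once per session, so no within-week time factor exists. Nor is the random-effects structure at fault: random effects are promised, and their detail may sit in the full plan.

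**Conclusion.** The stated inference is wrong for a sustained difference in level, and it concerns the primary aim. In an LME the three-way coefficient is then exactly zero and the named test rejects at about 5% for any size of shift. That result rests on algebra alone. The two-way power (77% to 90% at 0.4 within-person SD) rests on assumed SDs and compliance and only illustrates what could be missed.

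The finding does not extend to effects that start late or build up, nor to every GAM coding. It does not show that the three-way term is useless: that term is the right test of a difference in time course. Nor does it apply to EEG waveforms, where an effect varying over milliseconds may be the object of interest. The defect is that one term is made to answer two questions, and the worked example cites the wrong one.

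**What to change.** In Statistical analyses, Study aim 1:

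- Name intervention × session as the test of differential change in level for self-reported PC (ESM and SART) and for HR/HRV, matching the primary outcome definition. Specify it as mean pre-to-peri change, with time centred in an LME, or as the parametric term in a GAM. Without centring, the LME coefficient is the difference at time zero rather than the average over the week.
- Keep intervention × session × time as a separately labelled test of dynamics.
- Correct the worked example on present-oriented thoughts so that it cites the two-way term.
- Include both terms in the Benjamini–Hochberg family.
- Report any Bayes factor for the specific term it concerns, so that support for no difference in time course is not read as support for no difference in level.

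The cost is wording and one more test per outcome in the multiplicity family. Design and data collection are unchanged.

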## Methods

### Design

To examine the differential effects of mindfulness and positive fantasizing in rMDD and ND participants, we designed an open-label intervention cross-over study in which participants received both a mindfulness- and fantasizing intervention, in randomized order. The study is conducted at the University Medical Center Groningen, the Netherlands. The study includes five phases after an initial screening that is used to determine study eligibility. Eligible participants undergo 1) an assessment of baseline characteristics using self-report questionnaires (T0); 2) pre-intervention measurement 1 including one week of baseline momentary measures using Experience Sampling Methods (ESM) ten times per day, cognitive task performance two times per day, 24-h measurements of impedance cardiography (ICG)/electrocardiogram (ECG), one-week actigraphy measurements and an EEG lab measurement and questionnaires in the lab (T1); 3) peri-intervention measurement 1 where participants practice daily with an intervention and undergo the same measurements as in pre-intervention measurement 1 (T2); 3) pre-intervention measurement 2, which takes place after a wash-out period of at least one month consisting of one-week momentary measures, two-times daily cognitive task performance, actigraphy, 24-h of ICG/ECG, and EEG measurements and questionnaires in the lab (T3); 4) peri-intervention measurement 2, including practicing with the not-yet-performed intervention and the same measurements as in pre-intervention measurement 2 (T4). An overview of the study design can be found in Fig. 1.

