#### Exclusion criteria

Furthermore, individuals who meet any of the following criteria are excluded from participation in this study:Fulfilling criteria for any current DSM-5 diagnosis as objectified with the Structured Clinical Interview for DSM-5 (SCID-5) [48];Daily use of anti-depressive medication, benzodiazepines, methylphenidate, beta blockers or other medication potentially influencing ICG/ECG currently or in the last four weeks;Recent engagement (defined as in their last episode, or as one year prior to inclusion in case the last episode was more than a year before inclusion) in PCT including the positive fantasizing technique and/or have recent experiences (defined as daily practice in the past two years for at least two weeks) with mindfulness, meditation, or mindful yoga. This criterion prevents underestimation of true effects of the interventions and maximizes treatment effects;Participation in another clinical intervention study at the moment of inclusion in the study to prevent overlapping intervention effects.

Individuals for the ND control group who additionally meet any of the following criteria are excluded from participation in this study:Presence of symptoms of depression according to the IDS-SR30 (score > 13), to make sure they are not currently experiencing clinically relevant depressive symptoms;Any life-time psychopathology of any disorder as objectified with the SCID-5.

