### Sample size

To our knowledge, we are the first to combine ESM, ICG/ECG measures, and laboratory EEG measures to study the effects of different interventions on PC. It is difficult to do power calculations for our study since there is no software available that can make predictions for our chosen statistical methods (linear mixed effect models & generalized additive models; see Statistical Analyses). We therefore calculated the sample sizes using G*Power (version 3.1.9.4) for t-tests based on questionnaire measures.

In order to study the differential effects between mindfulness and positive fantasizing on PC in individuals vulnerable for depressive relapse, we will include 50 rMDD participants. In a meta-analytic review, Perestelo-Perez et al. [49] compared the effects of Mindfulness-Based Cognitive Therapy with usual care on rumination in patients with a current depressive disorder or a depressive disorder in the past. They observed a Hedges’ *g* of -0.59 for the effect of Mindfulness-Based Cognitive Therapy compared to usual care in reducing ruminative thinking. Using G*Power 3.1.9.4, sample sizes based on these outcomes were calculated. We expect PC to reduce after mindfulness and positive fantasizing. Therefore the sample size for one-tailed t-tests was calculated. To conduct one-tailed t-tests with a statistical power of 80%, the sample size should be *n* = 36 participants. A sample size of *n* = 50 rMDD participants should therefore give sufficient power to draw reliable conclusions about treatment effects, especially since questionnaires are a less sensitive measure than most of the other measurements used in the current study (i.e., ESM, ICG/ECG and laboratory EEG). This relatively large sample size also helps us to buffer against inevitable data losses related to e.g., participants not completing all questionnaires or technical malfunctions of the physiological measurements.

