### Randomization

All participants receive both interventions, which intervention they receive first is pseudo-randomly counterbalanced across participants. Pseudo-randomization here means that individuals are randomized to either fantasizing or mindfulness as first intervention by order of inclusion. Specifically, every three weeks a new measurement session starts. Mindfulness and fantasizing alternate in three-week blocks. New sign-ups in this three-week block are allocated to mindfulness or fantasizing, in alternating order.

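### The cross-over models name neither period nor order, which costs precision if the pre-to-peri change differs between periods and adds bias if the two orders are unequal in size

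*Protocol article*

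**What the plan says.** The Design section of the protocol article describes an "open-label intervention cross-over study in which participants received both a mindfulness- and fantasizing intervention, in randomized order". Each intervention has a pre week and a peri week (T1 and T2, then T3 and T4). The second pair starts with "pre-intervention measurement 2, which takes place after a wash-out period of at least one month".

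Under Randomization, order is called pseudo-randomly counterbalanced, and the mechanism is given as "Mindfulness and fantasizing alternate in three-week blocks".

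Under Statistical analyses, three sets of model factors are named:

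- Aim 1, primary outcomes (LME or GAM): the expected finding is an "interaction effect between intervention (fantasizing or mindfulness), session (pre- or peri-intervention), and time (time of ESM beep"). For the physiological outcomes, time runs from minutes to milliseconds.
- Aim 1, questionnaires (secondary outcomes): a repeated measures ANOVA with "intervention (fantasizing or mindfulness) and session (pre- or peri-intervention) as independent variables".
- Aim 2: the same models with group added.

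The only random effect mentioned is individual variability. Period, sequence, order and carry-over are not mentioned as model terms or as checks. The Sample size section says that 50 participants help to buffer against "inevitable data losses related to e.g., participants not completing all questionnaires".

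**The concern.** In a two-period cross-over, the intervention contrast within a person is also a contrast between the first and the second period. Both interventions are taught skills, and T3 and T4 repeat a demanding measurement schedule. The second training week may therefore produce a different pre-to-peri change from the first, whichever intervention is given. A model without period has two problems if so:

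- The period difference goes into the residual variation of the within-person contrast, and power falls.
- If more participants have one order than the other, part of the period difference is counted as an intervention difference.

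The time factor in the primary models does not deal with this, because it is time within a week or a recording and not the cross-over period.

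A separate and smaller matter is the questionnaire analysis. A classical RM-ANOVA usually uses only participants with all four sessions, whereas the LME already planned for other outcomes can keep those with some sessions missing.

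**Working it through.** **The plan's own figure.** This point contests no stated figure. The nearest is n = 36 for the rMDD group (g = 0.59, one-tailed, 80% power). It reproduces as an independent-groups test: 2 × (1.645 + 0.842)² / 0.59² = 35.5, so 36 per group (37 with the exact t distribution). A paired or one-sample one-tailed test would need 20. The figure is therefore not a yardstick for the number of within-person completers.

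**Set-up.** Let D be a participant's change under one intervention minus the change under the other, with SD 1 within each order. Let τ be the true intervention difference and π the amount by which the pre-to-peri change differs between the periods. Then D has mean τ + π in one order and τ − π in the other. N = 50 comes from the Sample size section. The values of τ, π, the order splits and the carry-over are assumptions, because the article gives none.

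**What cancels.** A shift that affects the pre and peri weeks of a period equally drops out of the change score. Only a period effect on the change itself (period × session) enters π.

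**Formulas for the analysis without a period term** (f is the share of participants in the first order):

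- Bias = π × (n1 − n2) / N
- SD inflation = √(1 + 4π²f(1 − f))

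At π = 0.5:

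| Order split | Bias (SD) | SD inflation |
|---|---|---|
| 25/25 | 0 | √1.25 = 1.118 |
| 27/23 | 0.5 × 4/50 = 0.04 | 1.117 |
| 30/20 | 0.5 × 10/50 = 0.10 | 1.114 |
| 33/17 | 0.5 × 16/50 = 0.16 | 1.107 |

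**Simulation** (20,000 runs, two-sided 5% test). The unadjusted mean of D is compared with the period-adjusted estimate, which is the mean of the two order means.

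| Split | τ | π | Rejection rate, no period term | Rejection rate, with period term |
|---|---|---|---|---|
| 25/25 | 0.4 | 0 | 79.4% | 79.3% |
| 25/25 | 0.4 | 0.5 | 71.9% | 79.2% |
| 25/25 | 0.4 | 1.0 | 49.8% | 79.6% |
| 25/25 | 0 | 0.5 | 2.8% | 4.9% |
| 30/20 | 0 | 0.5 | 7.4% | 5.1% |
| 33/17 | 0 | 0.5 | 14.3% | 5.0% |

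The term costs almost nothing when there is no period effect (first row).

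**Carry-over.** If the first intervention lowers the second-period change by λM after mindfulness and λF after fantasizing, the bias at 25/25 is (λM − λF)/2. With 0.3 after one intervention only, the bias is 0.15 and the type I error about 17% to 18%, with or without a period term. Equal carry-over of 0.3 gives no bias.

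**Questionnaires.** If only complete participants are kept and loss is independent across the four sessions, 50 × 0.95⁴ = 40.7 (about 41) remain at 5% loss per session, and 50 × 0.90⁴ = 32.8 (about 33) at 10%.

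**Limit of the check.** These figures are for the person-level intervention × session contrast. They do not simulate the full LME or GAM with beep time.

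**The case against.** The design already does much of the work. Order is counterbalanced, each period has its own baseline, and the second baseline follows a wash-out. With equal orders, leaving out period adds no bias and makes the test conservative. The 30/20 split is assumed, and at 27/23 the bias is only 0.04. The Randomization section also says that sign-ups within a block are allocated in alternating order. If that means person by person, the orders would be nearly equal at entry and only dropout could unbalance them. All of this stands, and it limits the size of the point.

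It can also be said that the article states which interaction is expected, not a full model formula, and that adjustment terms may sit in an analysis plan that is not shown. That is possible. But the article does choose and name its factors and its questionnaire method, so a reader is entitled to comment on the choice.

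Several stronger readings are tempting, but the documents do not support them:

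- **Data loss from the RM-ANOVA harms the main contrast.** It covers only secondary questionnaire outcomes. The primary outcomes use LME or GAM, which can keep partial data. That incomplete participants are dropped is also an inference from usual practice, not a statement in the article.
- **About 33 completers would fall below the planned 36.** The 36 is a per-group number for independent groups, so the two are unlike. The loss rate is also assumed: if the same five people missed every session, loss would again be 10% per session, yet 45 would remain.
- **T3 was collected to test the wash-out.** The article describes it only as the pre-intervention measurement for the second intervention.
- **The exclusion rule shows that the wash-out is too short.** That rule concerns mindfulness practice "defined as daily practice in the past two years for at least two weeks". The trial's own exposure, one two-hour session and six 10-minute exercises per intervention, is below that threshold.
- **A carry-over term is missing.** In a two-sequence, two-period design, carry-over is confounded with sequence, so such a term would not be a clean remedy.

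**Conclusion.** The point holds as a moderate and easily repaired weakness in the named models. Under equal orders it is a matter of precision: at an assumed period effect of 0.5 SD on the change and a true effect of 0.4 SD, power is about 72% without and 79% with a period term. Under unequal orders it is also a matter of bias, equal to the period effect times the relative imbalance, for example 0.10 SD at 30/20. If the change does not differ between periods, nothing is lost either way. Differential carry-over is possible, but neither shown by the documents nor removable by a period term. The questionnaire method is a separate, secondary matter whose size depends on a loss rate that the article does not give.

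**What to change.** 1. In the LME and GAM models for aims 1 and 2, add period, period × session and order as fixed effects.
2. For the secondary questionnaire outcomes, replace the RM-ANOVA with the same LME, so that participants who miss a session still contribute.
3. Report T3 minus T1 by first intervention with a confidence interval, and a sensitivity analysis restricted to the first period. Present both as descriptions of possible carry-over, not as a test that decides which analysis is used.

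The cost is a few degrees of freedom, a few lines of text and no new data. Data collection was still under way when the article was written, so the change could be fixed before analysis.
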